#### Moderators of outcomes

The trial will evaluate the following as potential moderators for the primary and any secondary outcomes that are significantly different between arms: age, type of probation, length of probation, anxiety measured by the SCL-90-R, Axis II comorbidities measured by the SCID, p factor scores derived from a bi-factor analysis of the self-report outcome measures, baseline alcohol use measured by the AUDIT, and baseline drug use measured by the DUDIT.

Moderators will be tested by including interaction parameters in the model and testing them for significance.

#### Mediators of outcomes

We will test the following as mediators (if there is a significant difference between arms in the mediating variable): alcohol use (AUDIT score); drug use (DUDIT score); mood (scores on the anxiety and depression subscales of the SCL-90-R); mentalizing (Brief Reflective Functioning Questionnaire score).

We will also test the proportion of MBT planned sessions attended as a post-baseline effect modifier (as it is only collected in the MBT arm).

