### Sample size and power calculation

The sample size (*N* = 302) has been chosen to have 90% power, at a two-sided 5% significance level, to detect a significant difference between groups when the change in OAS-M score is on average 10 points less in the MBT arm (with a standard deviation of 20) at the primary endpoint 12 months after randomization. Hollander et al. [68] reported the pooled standard deviation of the change in OAS-M score from baseline to 10-week follow-up as being just over 9 for the pharmaceutical intervention assessed in that study. Due to the longer follow-up period of the present trial and the non-pharmaceutical nature of the planned intervention, we have chosen to increase the standard deviation used in our power calculation to 20. To take into account potential clustering by clinician in the MBT arm, we assume the intraclass correlation coefficient to be 0.05. In this case, using established methods to take account of clustering [69], 95 participants per arm will give 90% power. We anticipate attrition and dropout to be 37%, based on several sources including our own preliminary work and several larger data sources (a meta-analysis of attrition rate in offender treatment literature [70], a systematic review of non-completion of treatment for personality disorder [71], and an empirical evaluation of treatment disengagement in offenders with personality disorder [72]). To account for this loss, initial recruitment of 151 participants per arm is anticipated to result in 95 participants remaining per arm after attrition and dropout. Our target sample size is therefore 302 participants, which will give sufficient power to detect a medium effect size of 0.5 change in participants’ OAS-M score.

Demographic and clinical details from those refusing randomization will be retained to explore whether the trial population is representative. To assess treatment acceptability, we will compute the proportion of referred individuals who never attended, the number of sessions attended, and the number who drop out of treatment or request to be referred to other treatments. All participants who do not formally withdraw from the study will be followed up on routine measures of outcome.

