*Drug use*, which is similarly linked to aggression and offending [88], will be measured by the Drug Use Disorders Identification Test (DUDIT) [89], which assesses frequency of use, indicators of dependence, and adverse consequences suggesting harmful use. The DUDIT has several advantages over other instruments, including a brief administration time (5 min) and its focus on recent use and consequences.

*Self-harming behaviours*, an indicator of impulsivity and a target of MBT, will be measured by the Self-Harm Inventory [90], a widely used measure that yields a severity of self-harm score based on the frequency of a wide range of impulsive behaviours.

*Suicidal behaviour*, a further complication of offending behaviour with ASPD [91], will be measured by the Suicidal Behaviours Questionnaire-Revised [92]. This instrument assesses four different dimensions of suicidality, including frequency of suicidal ideation and threat of suicide attempt.

*Health-related quality of life* will be measured by the EQ-5D-5L [93, 94]. The EQ-5D-5L is a standardized instrument for use as a measure of health outcome that is applicable to a wide range of health conditions and treatments. In this study, it will be used to provide a generic measure of health for both clinical and economic appraisal.

*Mental health status* will be measured by the Symptom Checklist-90 – Revised (SCL-90-R) [95]. The SCL-90-R assesses psychological distress in terms of nine primary symptom dimensions, including depression, anxiety, hostility, and paranoid ideation—all potential drivers of aggression.

*Personality dysfunction* will be measured by the Personality Inventory for DSM-5 – Brief Form (PID-5-BF) [96]. This 25-item personality trait assessment scale assesses negative affect, detachment, antagonism, disinhibition, and psychoticism and will provide a means of assessing change in the trait domains that are most prominent in ASPD.

*Categorically defined ASPD* will be measured by the ASPD module of the SCID-II, to assess whether MBT produces remission in ASPD diagnostic status.

*Mentalizing capacity* will be evaluated by the 16-item Brief Reflective Functioning Questionnaire [97] to assess whether MBT’s proposed mechanism of change is in line with any symptomatic improvements.

*Rates of desistance* will be measured by the Redemption and Condemnation Self-Narrative Scale version 2 to assess whether MBT increases rates of desistance in the participants.

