**ASSESSMENTS**											
**Questionnaires—participant**											
Overt Aggression Scale – Modified			x	x	x	x	x	x	x	x	x
EQ-5D-5L			x		x		x		x		x
Symptom Checklist-90–Revised Short Form			x		x		x		x		x
Alcohol Use Disorders Identification Test			x		x		x		x		x
Drug Use Disorders Identification Test			x		x		x		x		x
State-Trait Anger Expression Inventory			x	x	x	x	x	x	x	x	x
MacArthur Community Violence Screening Instrument			x	x	x	x	x	x	x	x	x
Short Form of the Revised Conflict Tactics Scales			x	x	x	x	x	x	x	x	x
Self-Harm Inventory			x		x		x		x		x
Suicidal Behaviours Questionnaire – Revised			x		x		x		x		x
Secure Facilities Service Use Schedule			x		x		x		x		x
Personality Inventory for DSM-5-Brief Form			x		x		x		x		x
SCID-II, ASPD Module			x				x				x
Brief Reflective Functioning Questionnaire			x		x		x		x		x
Redemption and Condemnation Self-Narrative Scale version 2							x				x

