#### Primary outcome

The primary outcome (OAS-M) at the various follow-up times will be analysed using a hierarchical mixed-effects linear regression with baseline OAS-M, length of sentence for index offence, and the stratification factors used in the randomization (except for site) as fixed effects. Patient ID and site will be included as random effects. A treatment effect parameter for each follow-up time will be included, although the primary one of interest will be treatment effect at 12 months. Two-sided *p* values less than 0.05 will be classed as significant.

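### Mediation, including through mentalizing, is tested only for markers that differ significantly between arms, so the indirect effect is estimated and reported selectively

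*Protocol article*

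**What the plan says.** Under Mediators of outcomes, the protocol article states: "We will test the following as mediators (if there is a significant difference between arms in the mediating variable"). It lists alcohol use and drug use, then "mood (scores on the anxiety and depression subscales of the SCL-90-R); mentalizing (Brief Reflective Functioning Questionnaire score"). That makes five scores: AUDIT, DUDIT, SCL-90-R anxiety, SCL-90-R depression and the mentalizing questionnaire.

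Examining mediators is one of the trial's aims (Aims section). Under Self-report measures, the mentalizing questionnaire is included to see whether the treatment's "proposed mechanism of change is in line with any symptomatic improvements".

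Table 1 schedules "Brief Reflective Functioning Questionnaire" at T1, T3, T5, T7 and T9, that is at baseline and 6, 12, 18 and 24 months. AUDIT, DUDIT and SCL-90-R follow the same schedule. OAS-M is collected every 3 months, with the primary endpoint at 12 months.

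The only significance threshold given stands under the primary outcome analysis: "Two-sided *p* values less than 0.05 will be classed as significant". The Statistical analysis section refers to a separate SAP, which was not available for this review.

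**The concern.** Mediation is a question of estimation: how much of the treatment effect runs through the marker, and how precisely is that known? The plan answers it only for markers that first pass a significance test on the arm difference. That has two consequences.

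- A marker that misses the threshold gets no indirect effect and no interval, even where the data are compatible with a sizeable one.
- A marker that passes has an arm-to-marker estimate selected for being large. The same estimate is then multiplied into the indirect effect, which is overstated on average.

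Readers could take an absent mediation result as evidence against the mechanism and a reported one at face value. Because this is a rule written in the article, an SAP that follows the article would inherit it.

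**Working it through.** **The plan's own figure.** The article says "The sample size (*N* = 302) has been chosen to have 90% power, at a two-sided 5% significance level", for the case in which "the change in OAS-M score is on average 10 points less in the MBT arm (with a standard deviation of 20"), and "we assume the intraclass correlation coefficient to be 0.05".

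- Without clustering: n per arm = 2 × [20 × (1.960 + 1.282) / 10]² = 84.1, rounded up to 85.
- With clustering in the MBT arm only and m participants per clinician: n per arm = (1 + DE) × 42.03, where DE = 1 + (m − 1) × 0.05. At m = 6, DE = 1.25 and n = 2.25 × 42.03 = 94.6, rounded up to 95. The article does not state m; m = 5 and m = 7 give 93 and 97.
- Attrition of 37%: 95 / 0.63 = 150.8, rounded up to 151 per arm and 302 in total.

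The sample size reproduces and is not at issue. It supplies the 95 per arm used below. The article gives no figure for the mediation analysis.

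**Inputs for the condition.** n = 95 per arm; two-sided 5% (assumed to carry over from the primary analysis); true marker shift d in SD units. The article states no d, so a range of 0.2 to 0.5 is assumed.

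**Formulas.** For a simple two-arm comparison:

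- SE = √(2/95) = 0.145 SD, so the observed shift must exceed 1.96 × 0.145 = 0.284 SD.
- P(pass) ≈ Φ(d/SE − 1.96).
- Mean estimate given a pass ≈ d + SE × φ(1.96 − d/SE) / P(pass).

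At d = 0.3, d/SE = 2.07 and P(pass) = Φ(0.11) = 0.54. The mean estimate given a pass is 0.3 + 0.145 × 0.397 / 0.543 = 0.406, and 0.406 / 0.3 = 1.35.

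| Assumed shift (SD) | Fails, 95 per arm | Exaggeration if passed | Fails, 85 effective per arm | Fails, 151 per arm |
|---|---|---|---|---|
| 0.2 | 72% | 1.87 | 74% | 59% |
| 0.3 | 46% | 1.35 | 50% | 26% |
| 0.4 | 21% | 1.13 | 26% | 6.5% |
| 0.5 | 7% | 1.04 | 10% | 1% |

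The 85 column approximates clustering at m = 6 (95 × 2 / 2.25 = 84.4). The 151 column assumes no loss to follow-up.

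**Baseline adjustment.** If baseline and follow-up marker scores correlate at r, SE shrinks by √(1 − r²). For an assumed r of 0.5 to 0.6, SE is 0.126 to 0.116. The pass rate at d = 0.3 then rises from 54% to Φ(0.43) to Φ(0.62), that is 67% to 73%. At d = 0.4 it rises to 89% to 93%.

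**Carry-over to the indirect effect.** Simulation with 95 per arm, an assumed marker-to-outcome slope of 0.4 and no confounding gives:

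| Assumed shift (SD) | Estimate/truth with the condition | Estimate/truth without it | Indirect effect detected with the condition | Interval excludes zero without it |
|---|---|---|---|---|
| 0.2 | 1.88 | 1.02 | 28.4% | 28.8% |
| 0.3 | 1.34 | 0.99 | 54.1% | 55.5% |
| 0.5 | 1.03 | 0.99 | 92.5% | 92.6% |

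Detection with the condition means a significant arm difference and a significant marker-to-outcome path. Removing the condition removes the bias and leaves power almost unchanged.

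**What silence can hide.** An observed shift just below 0.284 SD has an upper 95% limit near 0.284 + 0.284 = 0.57 SD. Holding the slope at the assumed 0.4, that is an indirect effect of up to 0.57 × 0.4 = 0.23 SD. This is about 45% of the 0.5 SD planned for OAS-M, yet no indirect effect would be reported.

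**The case against.** Four points deserve weight.

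1. **The size rests on an assumption.** The article gives no expected effect on any mediator. At 0.5 SD the condition is passed in about 90% to 93% of trials with 4% to 6% exaggeration, and baseline adjustment helps further. This stands: the harm is material only for modest shifts. But 0.5 SD is the planning effect for OAS-M, not for a marker. The Discussion's preliminary figures, 55–65% attendance at group sessions and dropout of one third, make a smaller shift plausible.

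2. **The condition costs almost no power.** An indirect effect needs an arm-to-marker path in any case. This stands. The fault lies in what is estimated and reported, not in detection.

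3. **A reader might infer that a non-significant marker leaves the mechanism unreported.** The article does not support that. The markers are among the secondary outcome measures, and continuous secondary outcomes are analysed by mixed-effects regression with no significance condition. The arm effect on mentalizing is therefore planned for estimation either way. Only the indirect effect is withheld.

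4. **A reader might also infer that a 12-month marker will be used to explain 12-month OAS-M, leaving the direction of effect open.** The article does not say so. It is silent on which visits are paired, a detail commonly left to the SAP, and its schedule provides a 6-month marker ahead of the 12-month endpoint. This is a matter to confirm, not a fault.

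**Conclusion.** The point holds for the significance condition. It is a stated rule, it applies to part of a stated aim, and it selects on a component of the quantity being estimated. At 95 per arm, with a simple two-arm comparison at two-sided 5%, the indirect effect is withheld in 72% to 7% of trials as the assumed shift runs from 0.2 to 0.5 SD. Mean exaggeration among those reported falls from 1.87 to 1.04 times over the same range. Baseline adjustment would soften these figures and clustering would slightly worsen them.

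It would go too far to say without qualification that a real mechanism will usually be skipped or badly overstated, since that needs a true shift of roughly 0.2 to 0.3 SD, which the article neither states nor rules out. The primary intention-to-treat comparison is unaffected.

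**What to change.** Delete the parenthetical condition under Mediators of outcomes. State that the indirect effect will be reported with a confidence interval for every listed mediator, whatever the arm difference in that mediator.

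Confirm in the SAP that the main mediation analysis pairs the 6-month marker (T3) with 12-month OAS-M (T5), adjusting for the baseline marker and for earlier OAS-M (baseline and a visit up to 6 months). Baseline OAS-M alone may not be enough. In an illustrative simulation with no true mediation, where aggression at 6 months drove the marker at that visit (slope −0.5) and persisted to 12 months (slope 0.3 to 0.7), adjusting only for the two baselines still gave an apparent mediated share of 8% to 19%.

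The cost is a change of wording and a few more models on data already scheduled. The drawback of the 6-month pairing is that marker change after month 6 is not credited in the main estimate.

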#### Economic evaluation

Mean total costs for the two groups at 24-month follow-up will be compared using a regression model with baseline costs as a covariate, an approach used despite the likely skewed distribution of the data because of the importance of the arithmetic mean in using the results for policymaking [105]. To test the robustness of the normality assumption, bootstrapped confidence intervals for the regression model will be also be calculated [106]. Quality-adjusted life years (QALYs) will be calculated from EQ-5D-5L health status using UK values for utility status [107] and assuming a linear change in utility over time. A cost-utility analysis will combine costs with the QALYs, a cost-effectiveness analysis will combine costs with aggressive behaviour and incremental cost-effectiveness ratios, and cost-effectiveness acceptability curves will be generated. Sensitivity analyses will include a test of the impact of the intervention costs on the cost-effectiveness results, and the impact of missing data, tested using multiple imputation of missing cost items.

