#### Randomization and procedures to minimize bias

Following consent and baseline measures, a trial identification number will be assigned to eligible consenting participants and a recruitment ‘dam’ created behind which a participant pool will be built up, from which participants will be randomized to enable MBT groups to start. Once groups have started, sequential assignment will allocate participants to MBT or PAU in a 1:1 ratio. Randomization will be undertaken off-site, using a dynamic adaptive allocation algorithm [76] accessed by a secure web portal to the system held at NWORTH Clinical Trials Unit (CTU) and maintained by a statistician independent of the analysis and research teams to ensure blinding. Stratification will be by site, age (21–25; 26–39; 40+ years), probation order type (Community Sentence; On Licence Post-Prison), and time remaining on probation (less than 12 months; 12 months and over). Treatment site is included in the minimization stratification to control for differences between sites. To minimize bias that could arise from knowledge of treatment allocation, researchers will be blind to participants’ treatment. The allocation to treatment arms will not be modified unless the local principal investigator, with the agreement of the clinical supervisor or the Trial Steering Committee (TSC), identifies severe risks of adverse events (homicide, suicide, serious injury, etc.) associated with the experimental treatment. Experimental treatment will be discontinued if the participant breaks the conditions of probation and is recalled to serve the remainder of their prison sentence for a time which prevents any further attendance or if the participant commits further offences and receives a custodial sentence for the fresh conviction that is longer than the remaining time of treatment.

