#### Economic evaluation

Health economic analysis will be conducted by King’s Health Economics at the Institute of Psychiatry, Psychology and Neuroscience, King’s College London, and will explore the relative costs and cost-effectiveness of MBT+PAU versus PAU. Although there is a preference for economic evaluations carried out on NHS services to take an NHS and personal and social services cost perspective, as recommended by NICE [99], in this case our primary analysis will take a wider societal perspective, including all healthcare, social and personal services, voluntary sector services, costs to the criminal justice sector, including probation, and the costs resulting from any crimes committed. The wider perspective is relevant and valid here because the interventions being compared are delivered in a criminal justice setting and the hypothesized impact will fall across both healthcare and criminal justice. A secondary analysis will consider the NHS/personal and social services costs only. Data on MBT contacts will be collected directly from sites, to avoid participants revealing their group allocation to the researchers. Data on the use of all other services, including PAU, will be collected in interviews using the Secure Facilities Service Use Schedule [100]. This instrument has been adapted to the current study population to ensure comprehensive coverage and face validity. Information on criminal activity will be extracted from police records. The cost of the trial interventions will be calculated through a detailed micro-costing (or bottom-up) approach using standard costing methodology [101], which will involve estimation of the indirect time spent on individual cases, including preparation, meetings, telephone calls, and supervision, as well as detailed recording of direct face-to-face contact. Other unit costs will be sourced from routine sources for the unit cost year 2017–2018 [102–104].

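### The 24-month cost regression names baseline costs as its only covariate and leaves out the minimisation factors that the primary clinical model includes, which costs some precision but does not bias the comparison

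*Protocol article*

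**What the plan says.** In the protocol article, the Economic evaluation part of Statistical analysis says that mean total costs in the two groups at 24 months "will be compared using a regression model with baseline costs as a covariate". The section accepts skewed costs because the arithmetic mean matters for policy, and it adds a check: "To test the robustness of the normality assumption, bootstrapped confidence intervals for the regression model". No further covariate is named.

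For QALYs the section says how each value is built. They "will be calculated from EQ-5D-5L health status using UK values for utility status", "assuming a linear change in utility over time". It then says: "A cost-utility analysis will combine costs with the QALYs". It does not say how the QALY difference between arms will be estimated.

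Under Randomization and procedures to minimize bias, the factors are site, age (three bands), probation order type (two levels) and time remaining on probation (two levels). On site it says: "Treatment site is included in the minimization stratification to control for differences between sites".

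The Primary outcome part of Statistical analysis enters baseline OAS-M, sentence length and "the stratification factors used in the randomization (except for site) as fixed effects". Site and patient are random effects there.

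The Economic evaluation part of Assessments and outcome measures takes a societal cost perspective that includes "costs to the criminal justice sector, including probation".

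**The concern.** The primary research question under Aims has two halves, effectiveness and cost-effectiveness. The article gives the full covariate set for the first. For the second it specifies the endpoint, the type of model, one covariate and the bootstrap check, but not the factors on which allocation was balanced.

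Those factors should carry information on cost beyond baseline costs. Baseline costs look backward, whereas time remaining on probation helps to determine how much supervision is still to come, and supervision is in the cost total. The PAU section says that interventions depend on what is available locally, so site should matter as well.

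When allocation balances prognostic factors and the analysis omits them, the model charges their variation to random error although the design has already removed it from the comparison. Intervals are then wider than they need to be and tests run below their nominal level. The planned bootstrap does not cure this. It is aimed at non-normality, and ordinary resampling of individual men lets the mix of strata vary between arms again.

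**Working it through.** **Inputs from the documents.** The article states no SD, power or sample-size figure for costs or QALYs, so there is no economic figure to reproduce. The stated target is for OAS-M: 95/(1 − 0.37) = 150.8, so 151 per arm and 302 in total. It reproduces but does not bear on this point.

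**Assumptions.** R² is the share of cost variance, after baseline costs, that the four factors explain. I take 10% and 20%, with 5% as a low case. Allocation is taken to balance the factors fully, so the figures are upper limits for a given R². As a reference I take an effect that would have 80% power if the model's own standard error were correct, which is a noncentrality of 1.960 + 0.842 = 2.802.

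**True size of the nominal 5% test with the factors omitted.** The true standard error is √(1 − R²) times the model's, so size = 2[1 − Φ(1.96/√(1 − R²))].
- R² = 0.10: 1.96/0.949 = 2.066, size 3.9%
- R² = 0.20: 1.96/0.894 = 2.191, size 2.8%

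**Power.** The smaller true variance applies to the unadjusted test too, so its power is Φ(0.842/√(1 − R²)). Adjusted power is Φ(2.802/√(1 − R²) − 1.96).

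| R² | True size, unadjusted | Power, unadjusted | Power, adjusted | Interval width, adjusted/unadjusted |
|---|---|---|---|---|
| 0.05 | 4.4% | 81% | 82% | 0.97 |
| 0.10 | 3.9% | 81% | 84% | 0.95 |
| 0.20 | 2.8% | 83% | 88% | 0.89 |

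The last column is √(1 − R²). Partial correlations of 0.2 and 0.3 correspond to R² of 0.04 and 0.09, which give intervals 2% and 5% narrower.

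**QALYs, conditional only.** Table 1 has EQ-5D-5L at baseline and every six months to 24 months. Trapezoid weights in years are 0.25, 0.5, 0.5, 0.5, 0.25. With unit SD and an assumed equal correlation of 0.5 between visits:
- Covariance of QALY with baseline = 0.25 + 1.75 × 0.5 = 1.125
- Variance of QALY = 0.875 × 0.5 + 4 × 0.5 = 2.4375
- R² = 1.125²/2.4375 = 0.52, width ratio √0.48 = 0.69

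Equal correlations of 0.3 and 0.7 give ratios of 0.82 and 0.54. A correlation that starts at 0.3 and decays with time gives R² of 0.15 and a ratio of √0.85 = 0.92. This shows what baseline utility is worth as a covariate. It does not measure an error in the plan.

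**Choice of bootstrap.** Resampling within site and arm would use 13 × 2 = 26 cells, with 302/26 = 11.6 men each, or 190/26 = 7.3 if 95 per arm remain. Resampling within a cell of n men understates variance by about 1/n, so standard errors shrink by 1 − √(1 − 1/11.6) = 4% to 1 − √(1 − 1/7.3) = 7%. That is similar to the precision gained from the factors, but in the anti-conservative direction.

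**The case against.** The strongest case against is that this is a condensed article. All planned analyses are to be set out in a Statistical Analysis Plan that is not shown, and the text does not say that baseline costs will be the only covariate. The secondary-outcome section names no covariates at all, and nobody would conclude that those models are unadjusted. Conservative standard errors also do no harm to validity, the gain is modest, and the level of a 5% cost test matters little to an acceptability curve.

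Much of this stands. It limits the point to a small improvement. It does not remove the point, because the cost model is stated in some detail and the covariate it names is not the set used for the clinical half of the same question.

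A reader might go further in three ways that the documents do not support.
- **That QALYs will be left unadjusted for baseline utility.** The section describes how QALYs are calculated and is silent on the model for their difference. A condensed article commonly leaves that to the analysis plan or a health economics plan.
- **That the economic analysis ignores baseline values.** For costs it does not, since baseline costs are in the model.
- **That omitting the factors biases the cost difference.** Randomisation keeps it unbiased, and minimisation already limits imbalance on exactly these factors.

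**Conclusion.** The point holds for the cost model as a low-cost improvement. As stated, the regression does not name the factors used in allocation, although the primary clinical model includes them. The consequence is conservative standard errors and some lost precision, with neither bias nor inflated false positives. If the factors explain 10% to 20% of residual cost variance, intervals are about 5% to 11% wider than necessary and adjustment adds about 3 to 5 percentage points of power. The R² values are assumptions that the documents can neither confirm nor exclude, and near 5% the gain is negligible. For QALYs there is no stated error. Naming the covariates there aligns the two increments that feed the same cost-effectiveness ratio.

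**What to change.** In the Economic evaluation part of Statistical analysis:
- Add age group, probation order type and time remaining on probation as fixed effects, and site as a random effect, to the cost regression alongside baseline costs.
- State that the QALY difference is estimated with the same factors plus baseline EQ-5D-5L utility.
- Use these adjusted increments for the cost-effectiveness ratios and acceptability curves, and bootstrap within arm, not within site-by-arm cells.

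This takes two or three sentences and no new data, since every variable is already recorded. The downside is a few extra parameters in the cost model: two for age, one each for order type and time remaining, and one site variance, on about 190 to 302 men. Follow-up was still in progress when the article was written, and the analysis plan is to be agreed before the trial statistician sees unblinded information. If that still holds, the covariates can be fixed without any suspicion that they were chosen on results.
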